## ***Study Description***

### **Brief Summary:**

This study will evaluate the effect of providing access to GPT-4, a large language model, compared to traditional diagnostic decision support tools on performance on case-based diagnostic reasoning tasks.

**Condition or disease:** Diagnosis

**Intervention/treatment:** Other: GPT-4

**Phase:** Not Applicable

### **Detailed Description:**

Artificial intelligence (AI) technologies, specifically advanced large language models like OpenAI's ChatGPT, have the potential to improve medical decision-making. Although ChatGPT-4 was not developed for its use in medical-specific applications, it has demonstrated promise in various healthcare contexts, including medical note-writing, addressing patient inquiries, and facilitating medical consultation. However, little is known about how ChatGPT augments the clinical reasoning abilities of clinicians.

Clinical reasoning is a complex process involving pattern recognition, knowledge application, and probabilistic reasoning. Integrating AI tools like ChatGPT-4 into physician workflows could potentially help reduce clinician workload and decrease the likelihood of missed diagnoses. However, ChatGPT-4 was not developed for the purpose of clinical reasoning nor has it been validated for this purpose. Further, it may be subject to disinformation, including convincing confabulations that may mislead clinicians. If clinicians misuse this tool, it may not improve diagnostic reasoning and could even cause harm. Therefore, it is important to study how clinicians use large language models to augment clinical reasoning prior to routine incorporation into patient care.

In this study, we will randomize participants to answer diagnostic cases with or without access to ChatGPT-4. The participants will be asked to give three differential diagnoses for each case, with supporting and opposing findings for each diagnosis. Additionally, they will be asked to provide their top diagnosis along with next diagnostic steps. Answers will be graded by independent reviewers blinded to treatment assignment.

## ***Study Design***

**Study Type:** Interventional (Clinical Trial)

**Actual Enrollment:** 50 participants

**Allocation:** Block randomization with block sizes of 4, 6, and 8; stratified by resident and attending physicians. Randomization list was created by [name] using the Sealed Envelope program.

**Intervention Model:** Parallel Assignment

**Intervention Model Description:** The trial will be designed as a cluster randomized, two-arm, single-blind parallel group study.

Masking: Single (Outcomes Assessor)

Masking Description: The grading of responses will be performed by assessors blinded to participant identity and treatment assignment.

Primary Purpose: Diagnostic

Official Title: Diagnostic Reasoning With Large Language Model Chat Bots

Actual Study Start Date: November 29, 2023

Actual Primary Completion Date: December 30, 2023

Actual Study Completion Date: December 30, 2023

### ***Arms and Interventions***

| Arm                                                                                                                                                                                            | Intervention/treatment                                                |
|-------------------------------------------------------------------------------------------------------------------------------------------------------------------------------------------------------|------------------------------------------------------------------------------|
| Active Comparator: GPT-4

Group will be given access to GPT-4.                                                                                                                                  | Other: GPT-4

OpenAI's GPT-4 large language model with chat interface. |
| No Intervention: Usual resources

Group will not be given access to GPT-4 but will be encouraged to use any resources they wish besides large language models (UpToDate, Dynamed, google, etc). |                                                                              |

### ***Outcome Measures***

#### **Primary Outcome Measures:**

Diagnostic reasoning [Time Frame: During evaluation]

The primary outcome will be the percent correct (range: 0 to 100) for each case. For each case, participants will be asked for three top diagnoses and findings from the case that support that diagnosis and oppose that diagnosis. Participants will receive 1 point for each plausible diagnosis. Findings supporting the diagnosis and findings opposing the diagnosis will also be graded based on correctness, with 1 point for partially correct and 2 points for completely correct responses. Participants will then be asked to name their top diagnosis, earning one point for a reasonable response and two points for the most correct response. Finally participants will be asked to name up to 3 next steps to further evaluate the patient with one point awarded for a partially correct response and two points for a completely correct response. The primary outcome will be compared on the case-level by the randomized groups.

#### **Secondary Outcome Measures:**

Time Spent on Diagnosis [Time Frame: During evaluation]

We will compare how much time (in minutes) participants spend per case between the two study arms.

### ***Eligibility Criteria***

Ages Eligible for Study: Child, Adult, Older Adult

Sexes Eligible for Study: All

Accepts Healthy Volunteers: Yes

### **Criteria**

Inclusion Criteria:

Participants must be licensed physicians and have completed at least post-graduate year 2 (PGY2) of medical training.

Training in Internal medicine, family medicine, or emergency medicine.

Exclusion Criteria:

Not currently practicing clinically.

### **Power Analysis:**

With a total of 50 participants enrolled, 25 participants per group, we will have >80% power to detect a difference of the score as low as 8%, when comparing AI group to non-AI group using a mixed-effect model in a cluster-randomized design. This is based on the assumptions that we will have on average 4 cases completed per participant, standard deviation of score as 16.2%, ICC in the range from 0.05 to 0.15, and a type I error of 0.05, according to our preliminary data. Power analysis was performed on PASS software.

### **Statistical Analysis:**

Descriptive analysis will be performed by comparing participant characteristics by the AI and non-AI group. Frequencies and proportions will be reported for categorical variables, while mean and standard deviations will be reported for continuous variables. We will also report the median and interquartile range for continuous variables that are not normally distributed. Bland-Altman plot will be generated to identify potential outliers of the scores where discrepancy between the two graders are outside the normal range.

The analyses of the primary outcome will be at the case level, clustered by the participant under the intention-to-treat design. In the primary analysis, cases with completed responses will be included. We will first describe the means and standard deviations of scores that will be standardized to 0-100 as well as median and interquartile range of time spent on each case, in the overall cohort and by the GPT-4

group compared to the conventional resources only group. Box plot will be generated for visualization. To assess the impact of incorporating GPT-4 in the exam, we will further apply generalized mixed-effect models with a random-effect for the participant to account for the potential correlation between cases for a participant, as well as a random effect for cases to account for any potential variability in difficulty across cases. We will consider the following sensitivity analysis:

- 1) Include incomplete cases on the primary outcome.
- 2) Include past experience in GPT use as a covariate for adjustment
- 3) Instead of taking the mean of the scores of the two graders, we plan to randomly select one score from the two graders of each question that are discrepant and rerun the analysis. We will repeat this process multiple times to ensure consistency.

Subgroup analyses will be conducted in a similar fashion, stratified by training status and experience with ChatGPT. Scores for each question of the cases will be also compared descriptively by the two randomized groups.

In a secondary exploratory analysis, cases completed by GPT-4 alone will be treated as a third group with cases clustered in a nested structure of 3 attempts under a single participant. Using a generalized mixed-effect model, these cases will be compared to cases from real participants with each case considered as a single attempt under a single participant using a similar nested structure. Missing data is not expected given our study design. If it occurs, multiple imputation will be considered under the intention-to-treat design for the primary analysis.

All statistical analysis was performed using R statistical programming languages, v4.3.2 (R Foundation for Statistical Computing, Vienna, Austria). Statistical significance was based on a p value <0.05.

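### Allocation is stratified by resident versus attending, but the primary mixed model names no term for that factor; if training status predicts the score, the test is mildly conservative and a little precision is forgone

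*Protocol*

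**What the plan says.** Protocol, Study Design (Allocation): "Block randomization with block sizes of 4, 6, and 8; stratified by resident and attending physicians". Training status is the only stratification factor named.

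Protocol, Statistical Analysis: the effect of GPT-4 on the case score is assessed with "generalized mixed-effect models with a random-effect for the participant to account for the potential correlation between cases for a participant", together with a random effect for case to absorb differences in difficulty. No fixed effect for training status is mentioned. Past GPT experience is the one covariate named for adjustment, and it belongs to the second sensitivity analysis. Training status enters the analysis only as a subgroup factor.

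Protocol, Power Analysis: the trial size is given as "With a total of 50 participants enrolled, 25 participants per group". The claim made for that size is "we will have >80% power to detect a difference of the score as low as 8" percent. It rests on an average of four cases for each participant and on "standard deviation of score as 16.2" percent. Alpha is set at 0.05, and the correlation within participants is given as "ICC in the range from 0.05 to 0.15". Stratification does not enter the calculation.

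**The concern.** Blocking within residents and within attendings makes the two arms nearly equal in their mix of training levels. Any difference in score between those levels then contributes almost nothing to the true sampling variability of the arm comparison. A model without the stratum term does not know this. It counts the difference as ordinary variation between participants and carries it into the standard error.

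If training status predicts the score, the reported interval is therefore wider than the design warrants and the test rejects a true null less often than 5% of the time. What is at stake is calibration and a modest gain in precision. The effect estimate itself is not biased.

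**Working it through.** **Inputs from the Power Analysis section.** 25 participants per arm, m = 4 cases each, SD 16.2, difference 8 points, ICC 0.05 to 0.15, alpha 0.05 (sidedness is not stated; taken as two-sided).

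**Assumed, because the protocol gives no figure.** R², the share of between-participant variance explained by training status, is varied from 0 to 0.3. Strata are of equal size, with arms balanced within each. The stated SD and ICC are taken to include the training-status difference. As a simplification, the random case effect is not modelled separately.

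**Step 1: the plan's own figure, with no stratum term.**

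Variance of a participant mean = SD² × [1 + (m − 1) × ICC] / m, and SE of the difference = √(2/25 × that variance).

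- ICC 0.15: 16.2² × 1.45 / 4 = 95.1; SE = √(0.08 × 95.1) = 2.76; power = Φ(8/2.76 − 1.96) = 82.6% (81.1% with a t distribution on 48 df).
- ICC 0.05: 16.2² × 1.15 / 4 = 75.4; SE = 2.46; power = 90.3% (89.1% with t).

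The claim of more than 80% power reproduces across the ICC range without help from the stratum.

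**Step 2: the true SE under stratified allocation.**

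SE_true = √(2/25 × SD² × [ICC × (1 − R²) + (1 − ICC)/4]).

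At ICC 0.15:

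- R² = 0.1: √(0.08 × 262.44 × 0.3475) = 2.70
- R² = 0.3: √(0.08 × 262.44 × 0.3175) = 2.58

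The unadjusted model still reports about 2.76.

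**Step 3: consequences.** The SE excess is the model SE divided by SE_true, minus 1. Actual alpha = 2 × Φ(−1.96 × SE ratio). Unadjusted power = Φ((8 − 1.96 × SE_model)/SE_true). Adjusted power = Φ(8/SE_true − 1.96). The gap that corresponds to a given R² is √(R² × ICC × 16.2² / 0.25).

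| ICC | R² | Implied gap (points) | SE too large by | Actual alpha | Power, unadjusted | Power, adjusted |
|---|---|---|---|---|---|---|
| 0.15 | 0 | 0 | 0% | 0.050 | 82.6% | 82.6% |
| 0.15 | 0.1 | 4.0 | 2.1% | 0.045 | 83.2% | 84.2% |
| 0.15 | 0.3 | 6.9 | 6.9% | 0.036 | 84.2% | 87.3% |
| 0.05 | 0.1 | 2.3 | 0.9% | 0.048 | 90.5% | 90.7% |
| 0.05 | 0.3 | 4.0 | 2.7% | 0.044 | 90.9% | 91.7% |

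**Step 4: check by simulation.** Participant means for 50 participants (26 and 24 per stratum, assumed; arms balanced within stratum) were analysed with and without the stratum term, 40,000 runs per setting, at ICC 0.15.

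- Gap of 4 points: power 81.5% unadjusted and 82.7% adjusted; type I error 0.045 and 0.050.
- No gap: power 81.1% and 81.2%; type I error 0.050 with either model.

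**The case against.** The strongest objection is that the Statistical Analysis section describes random effects and never lists the fixed effects in full. Even the treatment term has to be inferred. A separate SAP, not at hand, may well name the stratum. This has some force: the protocol nowhere says that training status is excluded. But it is not silent on adjustment either. It gives the random effects with reasons, puts its one covariate adjustment in a sensitivity analysis and keeps training status for subgroups. A primary model without the stratum is the natural reading.

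The second objection is that nothing in the documents shows that residents and attendings score differently. Eligibility requires completion of at least the second postgraduate year, so the most junior trainees are excluded and a large gap cannot be presumed. This stands, and it makes the whole effect conditional.

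A reader might go further and infer that the omission costs power the trial was counting on, or leaves it underpowered. The documents do not support that. The sample size took no credit for stratification, more than 80% power holds without the term, and unadjusted power rises slightly with the gap. A reader might also take a large gap, such as 8 points, as the typical case. With equal strata that gap needs a variance of 0.25 × 8² = 16. The total between-participant variance is only 0.05 × 16.2² = 13.1 at ICC 0.05, so the gap is impossible there. At ICC 0.15 it would be 16/39.4, about 41% of that variance.

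Finally, the subgroup analyses by training status do use the factor, but they do not correct the standard error of the primary comparison.

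**Conclusion.** The point holds as a minor matter of calibration and efficiency. The design stratifies on training status and the primary model, as described, does not include it. At ICC 0.15, with training status explaining an assumed 10% to 30% of between-participant variance, the standard error is about 2% to 7% too large, actual alpha is about 0.045 to 0.036, and about 1 to 3 points of power are forgone. Over the same range at ICC 0.05 the loss is under 1 point, and with no difference between residents and attendings it is zero.

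The error is on the conservative side: no bias, no inflated type I error, and no shortfall against the stated power. Severity is low. The sizes rest on the assumed R², equal strata and near-exact balance within strata.

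**What to change.** Add one sentence to the Statistical Analysis section: the primary model for the case score includes randomised arm and training status (resident or attending, as recorded at randomisation) as fixed effects, with random effects for participant and case. Use the same term in any mixed model fitted for time per case; the protocol clearly specifies only descriptive summaries for that outcome. Keep the model without training status as a supportive analysis. If a separate SAP already includes the term, bring the protocol text into line with it.

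The variable is already recorded for randomisation, so no new data are needed. The cost is one of 48 degrees of freedom. If there is no gap, power at ICC 0.15 by the t calculation stays at 81.1%. The protocol already lists actual completion dates, so if results by arm had been seen before the change, the adjusted fit should be labelled as added afterwards.

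### Subgroup analyses are specified as the primary model repeated within strata, with no treatment-by-subgroup interaction named, so they give a p-value per stratum but no estimate of whether the effect differs

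*Protocol*

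**What the plan says.** The Statistical Analysis section sets the primary analysis as a mixed-effect model at case level, with random effects for participant and for case. It then states: "Subgroup analyses will be conducted in a similar fashion, stratified by training status and experience with ChatGPT". The ordinary reading is that the same model is refitted within residents, within attendings and within each level of ChatGPT experience.

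The section ends with one rule that makes no exception for subgroups: "Statistical significance was based on a p value <0.05".

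No interaction between treatment and subgroup is named anywhere in the protocol. Prior GPT use otherwise enters only as an adjustment covariate in a sensitivity analysis, and a main effect cannot show whether the treatment effect varies. The comparison with GPT-4 alone is called exploratory; the subgroup analyses are not.

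Training status is a randomisation stratum (Study Design, Allocation); ChatGPT experience is not. The protocol does not give the number of physicians expected in any subgroup, or the number of experience levels.

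**The concern.** A subgroup analysis is meant to ask whether the effect of GPT-4 access differs between, say, residents and attendings. Separate models answer another question, namely whether the effect differs from zero in each group. One stratum can fall below 0.05 and the other above it when the effect is the same in both, simply because each stratum holds only part of a 50-person trial. With unequal strata, the larger one tends to be significant because it is larger.

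The trial's stated purpose is to learn how clinicians use these models before they enter routine care. A report that GPT-4 helps only one training level, or only experienced users, could influence training and adoption. The plan as worded can produce that pattern from a uniform effect and supplies no estimate that would check it.

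**Working it through.** **Inputs** (Protocol, Power Analysis): "With a total of 50 participants enrolled, 25 participants per group"; "on average 4 cases completed per participant"; "standard deviation of score as 16.2" percent; "ICC in the range from 0.05 to 0.15"; a target difference of 8 points; type I error 0.05, taken as two-sided because sidedness is not stated. Stratum sizes are assumptions and are varied below.

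**Step 1. Reproduce the stated power.** With n participants per arm and 4 cases each,

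SE = 16.2 × sqrt(2 × (1 + 3 × ICC) / (4n)).

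For n = 25:
- ICC 0.05: 16.2 × sqrt(2 × 1.15 / 100) = 2.46
- ICC 0.15: 16.2 × sqrt(2 × 1.45 / 100) = 2.76

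The noncentral t distribution on 48 df gives power of 89.1% and 81.1%. The protocol's claim, "we will have >80% power", is reproduced.

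**Step 2. One stratum, assumed even split.** With n = 12.5 per arm, the SE is 16.2 × sqrt(2 × 1.15 / 50) = 3.47 at ICC 0.05 and 16.2 × sqrt(2 × 1.45 / 50) = 3.90 at ICC 0.15. On 23 df, power for 8 points is 59.7% and 50.2%. The effect detectable with 80% power within a stratum is 10.2 to 11.4 points.

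**Step 3. Chance that exactly one of two strata is significant when both have the same true effect.** The strata contain different people, so this chance is p1(1 − p2) + p2(1 − p1), which is 2p(1 − p) for an even split. At 8 points:
- ICC 0.05: 2 × 0.597 × 0.403 = 0.48
- ICC 0.15: 2 × 0.502 × 0.498 = 0.50

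**Step 4. Vary the split, with 8 points in both strata.** Figures are simulated with t-tests on participant means, 200,000 runs each.

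| Assumed participants per arm in the two strata | Power in each, ICC 0.05 | Power in each, ICC 0.15 | Exactly one significant |
|---|---|---|---|
| 12 / 13 | 58% / 62% | 48% / 52% | 48-50% |
| 17 / 8 | 74% / 41% | 64% / 33% | 55% |
| 19 / 6 | 79% / 30% | 69% / 25% | 60-61% |

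**Step 5. Vary the common effect, even split**, with the formulas of steps 2 and 3 (range over ICC 0.05 to 0.15).

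| True effect in both strata | Exactly one significant |
|---|---|
| 0 | 9.5% |
| 4 points | 28-32% |
| 6 points | 43-47% |
| 8 points | 48-50% |
| 12 points | 16-27% |

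**Step 6. The interaction test.** In the same simulations it falsely declared a difference in 4.9% to 5.1% of runs in every scenario. At an even split its SE is sqrt(2) × 3.47 = 4.91 to sqrt(2) × 3.90 = 5.52. The difference between strata detectable with 80% power is then 14.1 to 15.8 points.

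**The case against.** Four stronger readings are tempting, and the protocol does not support them.

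- **That effect modification will be judged by comparing significance between strata.** The protocol does not say how subgroup results will be interpreted. The p<0.05 sentence is a blanket closing rule, and repeating the analysis in a similar way may also cover the descriptive summaries and box plots. The harm needs an interpretive step that the text invites but does not prescribe.
- **That no interaction analysis is planned.** The statistical analysis plan is not at hand and could add one. What can be said is that the protocol names none. This is still more than silence, because the protocol does fix a stratified method and a significance rule.
- **That each stratum has 12 to 13 physicians per arm.** This is only the even-split assumption. The resident/attending split and the experience levels are not given.
- **That discordance is a coin toss for any common effect.** The rate is near one half only when the common effect is roughly the planned one. It falls on both sides, as step 5 shows.

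Two technical objections also carry some weight. The calculation leaves out the random effect for case. If 20-30% of the score variance were case difficulty (an assumption), stratum power at an even split would rise to 56-73% and discordance would be 40-49%, a modest change. And the interaction test has little power: for an 8-point difference between strata, 37% at an even split and ICC 0.05, falling to 21% at an 80/20 split and ICC 0.15 (normal approximation). It protects against a false claim but will seldom settle the question.

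The plan also deserves credit for naming only two factors in advance and for randomising within training status.

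**Conclusion.** The point stands in limited form. The protocol fixes stratum-by-stratum models under a general p<0.05 rule and names no interaction, so the specified analysis cannot estimate whether the effect differs between subgroups. If the strata are then compared, a spurious contrast is likely at the planned effect: 48-50% for an even split, and 55-61% for splits of 17/8 to 19/6 per arm.

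These figures rest on the protocol's SD, ICC range and cases per participant, on a two-sided 0.05 test, on two strata per factor with equal arms, on assumed stratum sizes, and on a true common effect of 8 points. The point concerns the interpretation of subgroup results only. The primary analysis, sample size and data collection are untouched.

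**What to change.** For each subgroup factor, fit one mixed model on all participants with treatment, subgroup and their interaction, keeping the random effects of the primary model. Base any statement about effect modification on the interaction estimate and its 95% CI. Show the stratum-specific estimates with CIs beside it, and label the subgroup analyses exploratory. If the statistical analysis plan already does this, bring the protocol wording into line with it.

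The cost is about two sentences and no new data. The downside is that the imprecision becomes visible: at an even split only differences of about 14-16 points between strata are detectable with 80% power, so subgroup claims will look weaker. That imprecision is present under the current wording too, but is not shown.
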